#### Procedure for unblinding if needed {17b}

This is an open-label trial. Therefore, this is not applicable to this study.

### Data collection and management

#### Plans for assessment and collection of outcomes {18a}

A standard case report form (CRF) will be used to collect details on medical history and clinical examination, as well as the medical prescription in each group. The CRF will be digitalized for each arm.

For this study, an algorithm with functionalities easy to be used by nurses working at primary health facilities will be developed and installed on tablets for testing. All the clinical information needed to make a clinical decision based on IMCI and GDT will be pre-recorded and digitalized for the study use.

In control arm, nurses will systematically collect and enter all information related to fever during physical examination in the e-CRF. This physical examination will be supported by the malaria RDT, which is the only diagnostic tool available at the primary health facilities.

In the RDT-DA arm, nurses will systematically collect and enter all information related to fever during physical examination in the e-CRF. This physical examination will be supported by the POC tests, left to the discretion of the nurses. The final diagnostic and the prescription will be also left at the discretion of the nurses.

In the e-Algorithm arm, nurses will systematically collect and enter all information related to fever during physical examination in the e-CRF. This physical examination will be supported by the POC tests. A program will be set up by combining clinical signs and symptoms as well as the results of the PoC tests and will be downloaded on tablets to guide the diagnosis and the prescription.

All enrolled participants will be followed up on day 7 to assess their health status as well as find out if they complied with the prescription.

If fever persists, the participant will be referred to see a pediatrician at CRUN for better care. All treatment provided will be collected as well as the outcomes of the diseases. Parents/legal guardian will be asked to report to the clinical study staff at the health facilities, all concomitant treatment administered to the participant during the follow-up.

#### Plans to promote participant retention and complete follow-up {18b}

This study is planned for 7 days follow-up and loss to follow-up could be an issue even if the risk is low. To prevent this and based on our previous experience, an anticipated 10% corrective measure has been allocated to this risk in the sample size calculation to prevent any loss of follow-up. An explorative research has been conducted to assess the factors that could facilitate the acceptability of the proposed algorithm at community level. However, study staff will insist on communication with community/parents/guardians before the enrolment in the study in order to improve knowledge and awareness of study tests as well as the purpose of the study.

#### Data management {19}

Appropriate individual case record forms (CRFs) will be developed for data collection. In control and RDT-DA algorithm arms, CRF will be digitalized for the data collection only. However, in e-Algorithm arm, the algorithm including two-step malaria RDT detecting *Pf*HRP2/*p*LDH and PoC tests for bacterial infection will be digitalized to assist the healthcare workers in the diagnostic and treatment process and give the final diagnostic and the treatment proposed. For this purpose, an electronic CRF (e-CRF) will be developed. Adequate procedures will be put in place to ensure accuracy, reliability, and consistency of electronic records in e-Algorithm arm. The data management system will include audit systems to independently record the date and time of operator entries and actions that create, modify, or delete electronic records. All the data will be backed up and archived periodically. To avoid any entry of inconsistency data, a data entry control has been integrated in the digitalization of the CRFs. Nevertheless, a system of management of queries has been set-up to generate systematically queries and addressed to the study clinician for correction if any.

#### Plans for collection, laboratory evaluation, and storage of biological specimens for genetic or molecular analysis in this trial/future use {33}

Several biological samples will be collected for the management of participants depending on the randomization arms. In addition, biological samples will be collected for malaria microscopy and molecular analysis with PCR, and microbiology tests. These works will be restricted to the assessment of the presence of *Plasmodium falciparum* and other bacterial species. No human genetic material will be analyzed. The samples collected could be used for other analyses in order to improve the diagnostic of febrile diseases and specific informed consent will be obtained from study participants for this.

### Statistical methods

#### Statistical methods for primary and secondary outcomes {20a}

An analysis plan of the data has been developed and validated by the participants of the first workshop of the project, prior to the recruitment of the first study participants. Briefly, statistical analysis will be presented by treatment group. Categorical variables will be summarized as proportion, and chi-square test or Fisher’s exact test will be performed. For continuous variables, they will be described by mean or median and compared by using Student’s *t*-test. The proportion of patients that meet the criteria of the primary outcome (proportion of recovered case and antimicrobial) will be presented by arm. This analysis plan could be revised according to events and in case of amendment of the protocol. The statistical analysis will be done with an appropriate data analysis software (STATA 14.1. and R).

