### Enrolment

#### Day 0: Screening visit/ sample collection

Informed consent: After an in-depth discussion with the study physician or a member of the study team, the parent/legal guardian of the potential participant will be asked to document his consent by signing an informed consent form. The signed informed consent form (or thumb-print whenever the patient or the parents/guardians are illiterate) must be obtained before any data or sample collection for the study is done. Patients/guardians who will not consent to let his/her child to be part of the study will receive the standard of care as recommended by the Ministry of Health of Burkina Faso.Randomization of study participants: Study participants will be randomized to routine, RDT-DA or e-Algorithm arm at a ratio of 1:1:1 using varying block size of 20, 30, or 40 subjects in random order. Randomization list will be prepared by the data management and (bio) statistic department of CRUN.Randomization of study participants into the three arms will be performed by a trained study staff, after checking the inclusion and exclusion criteria.Demographic data and medical history: Demographic data and a general medical history of past and present illnesses, including the intake of any medication in the past month, will be recorded to determine the characteristics of the study participants.Control and intervention armsControl arm:

In the control arm, participants will follow the routine standard of care for the management of febrile diseases according to the national guidelines. In this arm, HRP2 based malaria RDT will be the only diagnostic tool available for the management of the fever episode. The clinical assessment (history of presenting complaints and physical examination) will be performed by health facilities staff (nurses). Except malaria for which an RDT is available, the other prescriptions in this arm will be based on clinical signs and symptoms as defined in IMCI.RDT-DA arm

The clinical assessment of the participant (history of presenting complaints and physical examination) will be performed by the study nurses. In this arm, participants will benefit the two-step malaria RDT detecting *Pf*HRP2/*p*LDH for the diagnosis of malaria infection and PoC tests for the diagnostic of bacterial infections. Samples tested will be sent to the microbiology laboratory of CRUN for culture.

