### Sample size {14}

Sample size is calculated based on data collected in the Siglé and Pella health facilities’ consultation books. From these data collected in 2018 (January to December), the proportion of febrile children under 5 years presenting at the health facilities with febrile illnesses and who were prescribed antibiotic was 62.63%. The implementation of the algorithm is expected to reduce this proportion to at least 20%. In this study, the sample size is computed to a Bonferroni correction of alpha which is performed for multiple comparisons; therefore, an alpha level of 0.017 is chosen. Type II error was controlled at 20%, i.e., (*β* = 0.20 or 80% power). Based on these parameters, a sample size of 356 is required per arm. Hence, an overall sample size for the study is estimated at 1068 (3 × 356). Further assuming that 10% of the individuals will be lost to follow-up, an adjusted sample size of 392 children per arm is required. The final estimated sample size for this study is thus 1176 children.

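### The only test named for the binary primary outcomes is unadjusted and not tied to the comparisons behind the 0.017 alpha; adjusted algorithm-versus-control risk differences would be a modest, almost free improvement

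*Protocol article*

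**What the plan says.** The Outcomes section lists two primary outcomes: the rate of favourable outcome at day 7, and the proportions prescribed antimalarials and antibiotics at day 0. Both are proportions.

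For proportions, the section on statistical methods for primary and secondary outcomes states: "Categorical variables will be summarized as proportion, and chi-square test or Fisher’s exact test will be performed". Continuous variables come next: "they will be described by mean or median and compared by using Student’s" t-test, a two-group procedure. The proportions meeting the primary outcome are to be shown by arm. The section names no contrast, effect measure, confidence interval or covariate. It introduces itself as a short account of a fuller document: "An analysis plan of the data has been developed and validated by the participants of the first workshop of the project".

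The sample size section uses "a Bonferroni correction of alpha which is performed for multiple comparisons; therefore, an alpha level of 0.017 is chosen". It does not list the comparisons.

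On the data available, the Day 0 section says that "Demographic data and a general medical history of past and present illnesses" will be recorded. Age is an eligibility criterion, and facility and enrolment date follow from where and when the child is recruited. The same section describes 1:1:1 allocation in blocks of 20, 30 or 40 and mentions no stratification factor.

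**The concern.** The trial sets two distinct algorithms against routine care in a superiority design, so the reader needs two answers: how each algorithm compares with control, and by how much. A chi-square or Fisher test gives a p-value but no size of effect. Without a statement of which arms enter each test, the reader cannot tell which p-values are to be judged against 0.017.

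The second issue is efficiency. Table 1 plans 760 children at Pella and 416 at Siglé, and August to November supplies (189 + 203 + 176 + 168)/1176 = 736/1176 = 62.6% of enrolment. If prescribing differs by facility or season, an unadjusted comparison carries that variation as noise, together with any chance imbalance between arms. With no stratification by facility described, balance on facility is left to chance. At stake are some precision and a clear reading of the primary result. Validity is not in question.

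**Working it through.** **Inputs.** Control prescribing 62.63%, alpha 0.017 (taken as two-sided; the article does not say), power 80%, and n = 356 per arm, all from the sample size section. Enrolment of 416 and 760 comes from Table 1. The share of outcome variance explained by covariates (R²) is not in the documents; I assume 0.02 to 0.10, with 0.20 as an upper case.

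**1. Alpha.** 0.05/3 = 0.0167, rounded to 0.017. A divisor of three matches the three pairwise contrasts among three arms, although the article does not use that word.

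**2. The plan's sample size.** The stated reduction can be read as a 20% relative fall (to 0.8 × 62.63 = 50.10%), a 20-point fall (to 42.63%) or a fall to 20%. With pooled variance under the null,

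n = [z(0.9915)·√(2p̄(1−p̄)) + z(0.80)·√(p₁(1−p₁)+p₂(1−p₂))]² / (p₁−p₂)².

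For the relative reading, p̄ = 0.5637 and the difference is 0.1253:

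n = [2.387 × 0.7014 + 0.842 × 0.6957]² / 0.1253² = (1.674 + 0.586)² / 0.01569 ≈ 326 (342 with continuity correction).

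The 20-point reading needs 129 and the fall to 20% needs 27. None of these equals 356, but only the relative reading comes near it, so I use that one below. The later steps do reproduce: 356 × 1.10 = 391.6, rounded to 392, and 3 × 392 = 1176.

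**3. Unadjusted pairwise power at 356 per arm.**

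power = Φ{[(p₁−p₂)√n − 1.674]/0.6957} = Φ(0.991) = 83.9%.

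**4. Power with adjustment.** Treat adjustment as raising the effective sample size to n/(1−R²).

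| R² (assumed) | Effective n per arm | Power | n per arm giving the precision of 356 unadjusted |
|---|---|---|---|
| 0 | 356 | 83.9% | 356 |
| 0.02 | 363 | 84.7% | 349 |
| 0.05 | 375 | 86.0% | 338 |
| 0.10 | 396 | 88.0% | 320 |
| 0.20 | 445 | 91.8% | 285 |

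A separate simulation (4,000 trials per scenario, linear probability model with robust variance against a pooled z-test, all covariate effects assumed) agrees. Power rose from 83.5% to 85.1% and from 83.6% to 87.7% with moderate predictors, and from 84.0% to 90.6% with strong ones.

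**5. What R² facility alone could supply.** With w = 416/1176 = 0.354, R² ≈ w(1−w)D²/[p̄(1−p̄)] = 0.2286·D²/0.2459. A prescribing gap D of 10, 20 or 30 points between the two sites gives 0.01, 0.04 or 0.08. The documents give no such gap.

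**6. Larger effects.** At 42.63%, unadjusted power at 356 per arm is already 99.9%; at 20% it is effectively 100%. Adjustment then adds almost nothing to power.

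**7. Global versus pairwise test.** If both algorithm arms reached 50.10%, a single three-arm test on 2 degrees of freedom would have 87.9% power at 0.017, against 83.9% for one pairwise test. A global test would therefore not lose power, but it would not say which algorithm differs from control.

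**The case against.** The strongest objection is that the article summarises an analysis plan that is not shown. Contrasts, covariates and interval levels are commonly left to such a plan, and the summary does not rule them out. This stands as a limit: the point improves on the one method that is stated, and it is no evidence that the final analysis will be unadjusted.

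A reader might infer that the analysis is a single three-group chi-square test. The text does not say so. The neighbouring t-test compares two groups and 0.017 fits three pairwise tests, so the documents lean towards pairwise testing. What remains is that the link is not stated.

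A reader might also infer that facility, season, age and temperature are strong predictors of prescribing. Table 1 gives attendance and enrolment targets only, with no prescribing rates, so plausible is the most that can be said. Nor is it stated that temperature or fever duration is kept as a pre-randomisation value for every child. Fever measured at presentation is one of two entry routes, the other being a history of fever.

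Finally, the unadjusted test is valid, power already exceeds the target "Type II error was controlled at 20"% implies, and blocking limits imbalance over calendar time. All of this is right. It makes the gain modest but does not remove it, because facility is not described as a stratification factor and the test still yields no effect estimate.

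**Conclusion.** The point holds as a low-severity improvement. The article names an unadjusted test for its binary primary outcomes, does not tie it to the comparisons for which alpha was set, and offers no estimate of the algorithm-versus-control difference. Nothing in it is invalid.

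The efficiency gain is about 1 to 4 points of power at 356 per arm (from about 84% to 85–88%). It rests on two assumptions that the documents do not settle: that the covariates explain 2% to 10% of outcome variance, and that the intended effect is 62.63% versus 50.1%. A gain to about 92% needs an R² of 0.20, for which there is no support in the documents. Naming the contrasts and reporting an effect with its interval is worthwhile whatever the gain in power.

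**What to change.** In the analysis plan, or by confirming that it already does so:

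- Name the contrasts (e-algorithm versus control, RDT-DA versus control) and test each at 0.017.
- For each, report the risk difference and risk ratio with a 98.3% confidence interval (100 − 1.7), from a binomial or robust-variance regression.
- Adjust for facility, enrolment month or malaria season, and age. Add axillary temperature only if it is recorded before randomisation for all children.
- Do not adjust for malaria RDT results: they arise after randomisation and come from different tests in control and intervention arms.
- Keep the chi-square or Fisher test as a sensitivity analysis.

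The cost is a few lines of text and slightly more programming. No new data are needed for facility, month and age.

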#### Interim analyses {21b}

Interim analyses are not planned.

#### Methods for additional analyses (e.g., subgroup analyses) {20b}

Next to the assessment of the proposed algorithm combining two-step malaria RDT detecting *Pf*HRP2/*p*LDH and PoC tests for bacterial infections, a social science investigation and an economic evaluation of the intervention will be conducted to identify the bottlenecks of the implementation of the point-of-care tests at primary health facilities level and the cost-effectiveness analysis of the intervention.

#### Design of social science investigation

The social sciences investigation will be focused on the adherence of healthcare workers to the algorithm (RDT-DA and e-Algorithm) as well as their prescription and patients/guardians’ adherence to the treatment prescription. The social science investigation will occur in two phases.

#### Phase 1: Exploration research

This research will occur immediately months 4 and 5) after the approval of the protocol by the ethics committee. The aim of this investigation will be to identify factors that may impact on the acceptability and feasibility of implementing the intervention (introduction of new POC tests) in the routine system, mainly among health care workers and parents/guardians.

*Study population*: To achieve the goal of this first step, three different populations will be considered for the qualitative data collection: healthcare workers, parents/guardians, and community members who are the main decision makers in the household.

*Sampling and sample size estimation*: Participants will be purposively selected and recruited from 3 selected populations based on some characteristics:The healthcare workers assigned by the MoH at the health center with at least two (2) years of experience. A maximum of 5 healthcare workers will be interviewed per site. This sample has been determined based on the number of nurses appointed at the health facilities of Siglé, Pella, and Bologo (maximum 5 nurses by health facility).The parents/guardians interviewed will be the ones attending the health facility with febrile children less than 5 years. A sample of 5 staff will be interviewed per site, which number can be reconsidered according to saturation of content principle.Two group discussions will be done with 16 community members, a group of 8 males and 8 females from the area where the health care center is located and who are the main decision makers in the household.

*Data collection tools*: Data (in-depth interview and discussions) will be audio recorded under the consent of the participants.

*Data analysis*: Data collected will be transcribed manually. NVivo software will be used for the management and the coding of data. During the analysis, key topics and concepts generated will be categorized.

*Outcome*:Primary outcome: Have a general overview of what can be an obstacle or strength for the study implementation.Secondary outcome: Create a good climate for study implementation.

#### Phase 2: Evaluation research

This research will occur during the study implementation. The aim of this investigation will be to analyze the adherence of health care workers and the community to the new algorithm. The participants will be interviewed on day 7 when they will come for the follow-up. This will help minimize forgetfulness.

*Study population*: The study population will be the healthcare workers who implemented the study in the different sites and the parents/guardians.

*Sampling and sample size estimation*: The healthcare workers who will participate in the study are those who implemented the study on the site (six nurses are expected for the two sites) and the parents/legal guardians of the study participants attending the recruitment sites (participants will be interviewed until the saturation of content is reached).

*Data collection tools*: Data (in-depth interview) will be audio-recorded under the consent of the participants.

*Data analysis*: Data collected will be transcribed manually. NVivo software will be used for the management and the coding of data. During the analysis, key topics and concepts generated will be categorized.

*Outcome of the investigation*:Primary outcome: Analyze the adherence of parents/guardians and health care workers to the algorithm.

#### Conception of health economic survey

The objective of the health economics component is to estimate the cost-effectiveness ratio of the proposed algorithm compared to the detection practices in place in the health facilities of the Nanoro health district.

#### Specific objectives

Estimate the cost of the proposed algorithm in the health facilities of the Nanoro health district;Estimate the costs of routine practices used in health facilities in the Nanoro health district;Calculate the incremental cost-effectiveness ratio;Determine the most cost-effective algorithm.

#### Methodology

*Type of survey*: A prospective study will be implemented to evaluate the cost effectiveness of the proposed algorithm in comparison with the routine algorithm in health facilities.

*Study sites*: The study sites are those of the e-MANIC study, namely the health centers of Siglé and Pella.

*Study perspective*: In Burkina Faso, children under 5 years of age are part of the UHC policy. So, all costs related to their healthcare are free of charge for parents/guardians. For that, we assumed that all costs were borne by the health facility, even those borne by the government such as salaries of health staff in each group (control and intervention). In short, our study perspective will be that of the care provider.

*Cost estimate*: To compare a medical intervention with another with the same objective, the most appropriate type of economic evaluation is a cost-effectiveness study. The two algorithms have the same efficiency indicator, namely the rate of cure and prescription of antimicrobials (antimalarials and antibiotics).

The approach taken for cost estimation is that of Larson et al. [22] which was used in a syphilis detection project in Zambia.

This approach proceeded by the inclusion of six parameters which are (1) the cost of the material per test, (2) staff time per test, (3) salary costs per test, (4) daily start-up and quality control costs, (5) cost of equipment, and (6) the average number of tests performed per day. Taking into account the type of algorithm used, we will make a selection of the parameters to include. Already, the costs of equipment such as scales, stethoscope, measuring tape, table, and chair were excluded because their costs are amortized. Additionally, building costs such as examination room, waiting room were also excluded for the same reason. The costs of electricity and the time-motion method will also be used to estimate the time spent to implement the diagnostic algorithms.

*Sample size*: All health facilities in the e-MANIC diagnostic study will be invited to participate in this ancillary study. Health workers from the study and health centers participating in the study will also be invited to participate in the study through interviews to assess the acceptability of the proposed algorithm.

*Collection tools and techniques*: Data collection will consist of observing consultations on the sites and administering a questionnaire based on an interview guide.

The observation technique will be used for the study of time motion. It will make it possible to estimate the time taken for a consultation using the proposed algorithm and in the routine. An observation grid will be developed for this purpose.

The oral interview technique will be used to collect the perceptions of health workers on the acceptability of the algorithm. To this end, individual interviews will be conducted. In addition, a questionnaire will be developed to collect information about the health facility.

*Data analysis*: Quantitative data processing software such as SPSS (Statistical Package for the Social Sciences) and Excel will be used. A data analysis plan will be developed.

The major costs of the different algorithms will be highlighted. The healing rates of each algorithm will be estimated and will serve as an efficiency comparator. The incremental ratio will be calculated according to the following formula:$$\frac{\mathrm{cure}\ \mathrm{rate}\ \mathrm{of}\ \mathrm{the}\ \mathrm{proposed}\ \mathrm{algorithm}-\mathrm{cure}\ \mathrm{rate}\ \mathrm{of}\ \mathrm{the}\ \mathrm{routine}\ \mathrm{algorithm}}{\mathrm{cost}\ \mathrm{of}\ \mathrm{the}\ \mathrm{proposed}\ \mathrm{algorithm}-\mathrm{costs}\ \mathrm{of}\ \mathrm{the}\ \mathrm{routine}\ \mathrm{algorithm}}$$

The data collected through the individual interviews will be transcribed. A transcription coding grid will be developed. A thematic analysis will follow.

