## Discussion

In Sub-Saharan Africa (SSA), acute febrile illnesses are one of the common reasons to seek medical care and are associated with considerable morbidity and mortality [23]. The introduction of malaria rapid diagnostic tests (RDTs) in the routine health care practice at the level of primary health care posts has considerably improved the management of malaria infection and reduced the unnecessary prescriptions of antimalarials. However, there is evidence that this positive development in malaria control program also has a downside due to an increases use of antibiotic in the malaria RDT negative group presenting with fever and this may threat the antibiotic efficacy. Moreover, this situation becomes exacerbated when the malaria RDTs used are still below the expected diagnostic performance in terms of sensitivity and specificity. It is then important to adapt the current practice at primary health facilities in the framework of universal health coverage (UHC) policy adopted by Burkina Faso.

This project has been designed to promote the evidence-based diagnostic for a better management of illnesses in malaria endemic area and reduce the unnecessary prescription of antimicrobials. The project will allow to assess the contribution of an algorithm involving two-step malaria RDT detecting PfHRP2 and pLDH supported by point-of-care tests (PoC tests) for bacterial infection in the management of acute febrile diseases and antimicrobial prescriptions. The project will contribute to (i) save lives by establishing the real cause of fever, (ii) reducing the high cost of treatment during fever episode, due to the inappropriate prescription of antibiotic, (iii) and tackling the antimicrobial resistance (AMR). The project is therefore in line with global effort for the achievement of SDG3 by Horizon 2030.

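### The stated cost inputs cover testing only: antimicrobials and unscheduled visits are not among them, so the incremental cost can be biased in either direction

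*Protocol article*

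**What the plan says.** Under Conception of health economic survey, the Methodology section adopts a costing approach "which was used in a syphilis detection project in Zambia". It lists the inputs: "This approach proceeded by the inclusion of six parameters which are (1) the cost of the material per test, (2) staff time per test", and then "3) salary costs per test, (4) daily start-up and quality control costs, (5) cost of equipment, and (6) the average number of tests performed" daily. It goes on: "Taking into account the type of algorithm used, we will make a selection of the parameters to include". Beyond the six it adds only this: "The costs of electricity and the time-motion method will also be used to estimate the time spent to implement the diagnostic algorithms". The exclusions it names are basic examination equipment, furniture and buildings.

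On viewpoint, the same section states that "our study perspective will be that of the care provider". The reason given is that care for under-fives is free to families, so the facility is assumed to carry every cost.

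The section names cure and antimicrobial prescription together as the efficiency indicator. The printed incremental ratio, however, has the difference in cure rate above the line and the difference in algorithm cost below it. Prescription does not appear in it.

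The Discussion lists among the project's contributions "reducing the high cost of treatment during fever episode, due to the inappropriate prescription of antibiotic".

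The trial's clinical data do contain the relevant quantities. The prescription in each arm is recorded in the case report form, and day-0 prescribing is a primary outcome (Outcomes {12}). Visits before day 7 are recorded as unscheduled visits. The section on outcome collection {18a} also says: "All treatment provided will be collected as well as the outcomes of the diseases".

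**The concern.** The algorithm arms spend more on tests in the hope of prescribing less without harming recovery. A provider-perspective comparison therefore needs at least three components: added testing, the change in drugs used, and any change in return visits. The stated inputs hold only the first. The perspective says that all of the children's care costs belong to the provider, but the input list leaves two of them out. Nor can the effect side compensate, because the ratio counts cures and not prescriptions.

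What is at stake is the choice of the most cost-effective algorithm, which Specific objectives sets as a goal, and the policy use that the Background foresees for the results. The drug saving named in the Discussion would have no monetary counterpart in the analysis meant to support it.

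**Working it through.** **1. Classify the stated inputs.**

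| Input | What it costs | Drug or return visit? |
|---|---|---|
| Material per test | testing | no |
| Staff time per test | testing | no |
| Salary per test | testing | no |
| Daily start-up and quality control | testing | no |
| Equipment | testing | no |
| Tests per day | volume of testing | no |
| Electricity (added) | delivery of the algorithm | no |
| Time-motion (added) | consultation time | no |

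None of the eight is a drug or return-visit cost, and selecting from the six cannot add one.

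**2. Write out the cost difference.** Per child, algorithm minus routine:

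- Stated inputs: ΔC = Δtesting + Δstaff time (with electricity).
- Provider perspective: ΔC = Δtesting + Δstaff time + Δdrugs + Δunscheduled visits.

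Δdrugs is negative if prescribing falls. Δvisits can have either sign. The error in the stated version is −(Δdrugs + Δvisits), whose sign is not known in advance.

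**3. Scale in courses.** The article gives no cost figure to reproduce, so this uses Sample size {14}: control rate 62.63%, alpha 0.017 (taken as two-sided), 80% power, 356 per arm analysed, 392 recruited. The usual formula with pooled variance under the null is

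n = [z(1−α/2)·√(2p̄(1−p̄)) + z(1−β)·√(p₁(1−p₁) + p₂(1−p₂))]² / (p₁ − p₂)²

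with z values 2.387 and 0.842. Setting n = 356 and p₁ = 0.6263 gives p₂ = 0.5066, a difference of 0.1197. Then 0.1197 × 392 = 47 courses per arm.

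The article's wording of the expected reduction can be read in three ways:

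| Reading | Difference | n per arm required | Courses avoided per 392 |
|---|---|---|---|
| 20% relative | 12.5 points | 326 | 49 |
| 20 points | 20.0 points | 129 | 78 |
| Down to 20% | 42.6 points | 27 | 167 |

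Only the first comes near 356, so 47 to 49 courses is the scale that fits the trial's own size.

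**4. Scale in money, by assumption only.** Let r be the price of one antibiotic course divided by the added testing cost per child. The article gives neither. The share of the test-only incremental cost that avoided antibiotics would offset is 0.12 × r:

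| r (assumed) | 0.25 | 0.5 | 1 | 2 | 4 |
|---|---|---|---|---|---|
| Share offset | 3% | 6% | 12% | 24% | 48% |

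**5. The opposite direction.** Let v be the cost of one unscheduled visit divided by the price of one course (also assumed). A saving of 12 courses per 100 children is cancelled by 12/v extra visits per 100: 12 extra visits if v = 1, and 6 if v = 2. Any change in antimalarial use would move the balance further either way.

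**The case against.** The strongest reply is that this is an article's summary of an ancillary study. It says that an economic data analysis plan and a facility questionnaire will be developed, and drugs are not among the named exclusions. It also sets out to cost routine practices and to time whole consultations. That stands against one tempting inference, that drugs will never be costed or that the project cannot show a saving. The later plan may add them, and the fall in prescribing will be reported as a count in any case. It does not remove the point. The article is not silent on cost inputs: it gives the list, says that it will be cut down, and names the additions. As stated, the list is incompatible with the stated perspective.

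A second reply is that the Discussion sentence is not an economic objective, and that the survey's aim refers to detection practices. This is fair as to the Discussion. But Specific objectives promises an incremental cost-effectiveness ratio and a choice between algorithms, and the ratio is set against cure, which depends on treatment.

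Further inferences that a reader might draw are not supported:

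- **That the incremental cost is overstated.** This holds only if the drug saving exceeds any added cost of return visits. Neither is known.
- **That up to 167 courses go uncosted.** That needs a fall to 20%, which about 27 children per arm would detect. It does not fit 356.
- **That all referrals are omitted provider costs.** Children still unwell are sent to the study clinician or to a paediatrician at the research unit. This is partly trial-driven care, and whether to include it is a judgement.
- **That per-test inputs prevent a per-child cost.** Unit costs can be multiplied by tests used.
- **That the source method was designed for a single screening test.** The article calls it only a syphilis detection project.
- **That all treatment in every child is certainly captured.** The sentence "All treatment provided will be collected as well as the outcomes of the diseases" follows the one on referral for persisting fever and may cover only those children. Prescriptions are recorded for every arm elsewhere in the same section.

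**Conclusion.** The concern holds as an inconsistency between the stated cost inputs and the stated perspective. Antimicrobials and unscheduled visits are in neither the six parameters nor the two additions, and prescriptions do not enter the effect side of the ratio. The incremental cost can therefore be biased in either direction.

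The scale is about 47 antibiotic courses per 392 children without a monetary value. This assumes a fall of about 12 points, which is back-calculated from 356 per arm at two-sided alpha 0.017 and 80% power and is not an effect the article states. The monetary error cannot be given, because the article contains no unit prices; the offset shares above rest wholly on an assumed price ratio.

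The analysis is ancillary, and no primary outcome or safety assessment depends on it. It should still be corrected before the economic analysis plan is fixed, because the ratio is to decide which algorithm is most cost-effective.

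**What to change.** Define one cost per child managed, identical in all three arms:

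(tests used × unit cost) + staff time + antimicrobials prescribed or dispensed on days 0–7 + unscheduled facility visits.

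Take test use, prescriptions and visits from the trial records, take staff time from the planned time-motion work, and apply a local price list for tests, drugs and a facility visit. Check that treatment after day 0 is recorded for every child and not only for those referred.

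State separately whether study-driven referrals are included, and whether the e-Algorithm's tablet, software and training costs are. The article does not show that the latter are collected, so they may need their own source.

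The core definition uses quantities already recorded and needs no new patient visits. The price is a local price list and a slightly larger costing exercise.
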